## Cluster Randomised Study.

The main study will be a cluster randomised trial conducted in two phases. Clinics will initially be randomised to one of two arms in the trial and then subsequently, clinics will be randomised a second time to two additional trial arms.

### Trial Arms:

**Phase I:**

*Arm 1: Non-intervention arm:*

The non-intervention arm will be based on the existing clinical diagnosis, pre-referral treatment and referral to a clinic in areas where RDTs have not been deployed at CHW level. Arm 1 CHWs will receive refresher training according to the National Strategy for CBMM which includes the current IMCI guidelines.

Vs:

*Arm 2: RDT Arm*

Provision of community level diagnostics by rolling out RDTs to CHWs through the national strategy for Community based Management of Malaria. The arm has been designed exactly as the current National guidelines for RDT implementation..The arm will include:

- Clinic level microscopy or RDT and CHWs using RDTs to provide parasitological diagnosis to diagnose, treat and/or refer patients. Under this scheme, CHWs will be provided with CQ, SP and artesunate (AS). Depending on the diagnostic result, they prescribe according to the National Treatment Guidelines (CQ for confirmed vivax, SP and AS for confirmed falciparum, and no antimalarial for a negative result).
- CHW training will be conducted exactly as described in the CBMM strategy, using a “trickle down approach” where Training of Trainers takes place at the central level for provincial trainers of local NGOS who run the health service. These, in turn, run workshops for training CHSs and CHWs (see section 2.2 for pre-evaluation of training and roll-out). Participants will receive training to enforce revised IMCI guidelines, taken from the CBMM strategy document, which include an RDT in the algorithm for fever (see annex 2).
- There are no plans for additional support or refresher training, and no plans for quality control and assurance contained in the National Plan.
- CHWs are not equipped with suitable storage facilities for the RDTs, for example evaporative coolers.
- Monitoring and evaluation takes place according to the draft strategy.

The second phase of the trial will be initiated in Feb 2012. The second phase of the trial will re-randomise clinics to either the RDT arm (as in arm 2, above) and a third arm (arm 3). The third arm will answer the question: “how can the performance of RDTs at community level be enhanced?”. The same set of outcomes will be used to measure the relative effectiveness of each approach. A revised random allocation using the same methods will be conducted for the Phase II randomisation.

**Phase II**

*Arm 2: RDT arm (as above)*

*Vs.*

*Arm 3: Extended Programme Rollout of RDTs:* The intervention arm will consist of an extended programme of implementation. The intervention is designed with the aim of providing a best-practice model for rollout of RDTs at community level. The intervention arm will consist of a range of supportive interventions alongside the RDT roll-out:

- Clinic level microscopy or RDT and CHWs using RDTs to provide parasitological diagnosis to diagnose, treat and/or refer patients. Under this scheme, CHWs will be provided with CQ, SP and artesunate (AS). Depending on the diagnostic result, they prescribe according to the National Treatment Guidelines (CQ for confirmed vivax, SP and AS for confirmed falciparum, and no antimalarial for a negative result).
- CHW training will be conducted by dedicated trainers. Cadres of CHWs for each clinic will be trained which will include several modules (basic febrile illness management and additional training on IMCI and use of RDTs within the IMCI guidelines, clinical practice in RDTs, prescription of antimalarial drugs, blood safety and sharps disposal, treatment of RDT negative patients) as well as practical training.
- CHWs will be provided with regular support to review their application of RDTs using case-studies.
- RDTs and CHWs will be actively involved in improved quality assurance and quality control procedures
- CHWs will be issued with evaporative coolers to store RDTs
- Other supportive interventions will be considered following the results of the initial survey, interim analysis of the social science components and phase 1 of the trial.

### Randomisation for Phase I:

In CRT with a small number of clusters (e.g. <15-20 per arm) and strong between-cluster correlation there is an increased chance of an imbalance on one or more covariates across the intervention arms. If these covariates are also expected to be important correlates of the primary outcome then this can influence the interpretation of the study results. Although imbalances may be adjusted for in cluster-level analysis there is some inadequacy in this approach and therefore Raab (2001) and Moulton (2004) suggest constraining the randomisation through restriction to those allocations that meet specified criteria, to achieve balance at the start. They suggest constraining enough so as to ensure marginal balance on relevant covariates.

### Balance criteria:

The following variables that are expected to be important correlates of the primary outcome and on which we wish to achieve balance were based on a data collected in 2009 in the same study clusters and over the same study period i.e. July to December.

1. Harmonic mean. For a given number of clusters and overall sample size maximum statistical efficiency is obtained if an equal number of patients per cluster are selected. The total sample size of 1500 across 22 clusters would require an *arithmetic* mean of 68 patients per cluster. However, due to the huge variability in the proportion of patients seen with suspected diarrhoea, URTI and malaria (when CHWs are likely to use RDTs) per cluster this approach was not seen as appropriate for several reasons including time to reach sample size quota, and cluster representation. Hence the sample size was weighted according to the cluster proportion of patients seen with suspected diarrhoea, URTI and malaria to achieve a *harmonic* mean of 68 patients per cluster in each arm. Since the sample size calculation was done before randomisation the overall harmonic mean (for all clusters) was used but this does not guarantee a harmonic mean of 68 per arm and therefore this was included as a restriction factor in the randomisation.
2. Total sample size. The precision and power of a study are usually maximised when sample sizes are similar in the treatment arms. In CRTs this means that the number of clusters as well as the number of individuals should be similar across treatment arms. Therefore, due to the variability in sample size per cluster this was also added as a restriction factor.
3. Number of health posts. There is a substantial amount of variation in the number of health posts per cluster from 2 to 26. Clusters (clinics) with bigger catchment populations have more health posts and therefore by balancing on this factor and equal sample size per arm will be achieved.

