### Final combination of balance criteria

The final choice included the following restrictions:

1. Total sample size per arm differing by no more than 50
2. Harmonic mean in each cluster being within the range 65 to 71
3. The number of health posts per arm differing by no more than 10 health posts

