### Baseline characteristics by study arm

It can be seen from **Table 4** that given the above restricted randomisation we achieved a suitable balance on those factors included in the randomisation. A baseline table showing all individual and cluster-level covariates would also be interesting to include in a paper to examine the balance on factors not included in the randomisation.

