### Trial Profile:

**Figure: Trial schematic for Phase 1.**

If the criteria for running phase 2 of the trial are met the 22 clinics will be re-randomised so that 50% of those clinics in arm 1 are randomised to arm 3 and 50% to arm 2, and 50% of those in arm 2 will be randomised to arm 3 with 50% remaining in arm 2 (figure 2).

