### Number of consultations per clinic and health post:

In the 22 study clinic, there are 207 health posts (414 community health workers). The sample size will be limited by the number of consultations where an RDT will be deployed. The table shows the monthly activities report for the Health Posts in the study clinics for 3 months, from July-Sept 2010.

| **Province/clinic** | **Number of Health Posts** | **Number of treatments given for:** | | | |
| --- | --- | --- | --- | --- | --- |
|  |  | **Malaria** | **URTI** | **Diarrhoea** | **Total** |
| **Kunduz** | **65** | **47** | **2693** | **3161** | **5901** |
| Ajighan | 6 | 3 | 267 | 345 | 615 |
| AngorBagh | 7 | 3 | 568 | 823 | 1394 |
| ArbabRamazani | 2 | 2 | 54 | 73 | 129 |
| BolaQachi | 5 | 10 | 246 | 268 | 524 |
| CharSari | 6 | 2 | 245 | 205 | 452 |
| Khan Abad | 20 | 0 | 560 | 584 | 1144 |
| KhwajaGhaltan | 8 | 6 | 264 | 387 | 657 |
| Madrasa | 3 | 17 | 131 | 103 | 251 |
| Nick Pay | 3 | 0 | 36 | 49 | 85 |
| SandoqSai | 5 | 4 | 322 | 324 | 650 |
|  |  |  |  |  |  |
| **Nangarhar** | **142** | **2471** | **3736** | **3611** | **9818** |
| Baro | 8 | 63 | 158 | 230 | 451 |
| Batikot | 21 | 450 | 541 | 468 | 1459 |
| Behsood | 16 | 216 | 354 | 297 | 867 |
| Chardhi | 6 | 45 | 112 | 93 | 250 |
| GardiGhos | 6 | 310 | 342 | 281 | 933 |
| Khewa | 12 | 158 | 487 | 670 | 1315 |
| LandaBuch | 10 | 174 | 258 | 247 | 679 |
| MamandDara | 11 | 382 | 319 | 313 | 1014 |
| NajmulQura | 6 | 189 | 291 | 329 | 809 |
| Rodat | 13 | 52 | 50 | 37 | 139 |
| SangarSarai | 18 | 212 | 271 | 338 | 821 |
| Shegay | 15 | 220 | 553 | 308 | 1081 |
| **Grand Total** | **207** | **2518** | **6429** | **6772** | **15719** |

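### The Phase I restriction factors, described as correlates of the primary outcome, are all size measures; within-province malaria burden was left uncontrolled, differs between the drawn arms, and should be adjusted for and added to the Phase II restriction

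*Protocol*

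**What the plan says.** Section 2.5.3 of the protocol presents the restriction factors as "The following variables that are expected to be important correlates of the primary outcome and on which we wish to achieve balance". The limits finally adopted in section 2.5.4 are:

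- "Total sample size per arm differing by no more than 50"
- "Harmonic mean in each cluster being within the range 65 to 71" (this can only sensibly be read as the harmonic mean in each arm)
- "The number of health posts per arm differing by no more than 10 health posts"

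Randomisation is stratified by province. After the draw, section 2.5.5 reports that "we achieved a suitable balance on those factors included in the randomisation" and leaves other covariates to a baseline table in a paper.

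Section 2.8.2 tabulates, clinic by clinic, the CHW treatments for malaria, URTI and diarrhoea in July–September 2010. One row reads "Batikot | 21 | 450 | 541 | 468 | 1459" (health posts, malaria, URTI, diarrhoea, total). In the randomisation, malaria enters only as part of that pooled volume, through the sample-size weights.

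For Phase II, section 2.5.1 says: "A revised random allocation using the same methods will be conducted for the Phase II randomisation". Section 2.5.6 adds that "50% of those clinics in arm 1 are randomised to arm 3 and 50% to arm 2", and likewise for the other Phase I arm. The explanatory variables sketched in section 2.8.4 include neither malaria burden nor province.

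**The concern.** The protocol's stated reason for restricting is to balance covariates that predict the primary outcome. The reasons it then gives for the three factors are statistical efficiency, precision and power, and equal sample size. It states no link from any of them to correct treatment.

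The outcome in section 2.6.1 does depend on malaria status, because the correct action differs for falciparum, vivax and negative patients. How much malaria CHWs see or treat in each clinic is therefore an obvious candidate for balance, and the figures were to hand. If the arms differ on it before any intervention, an unadjusted comparison of 11 clinics with 11 carries that difference along with avoidable between-clinic variance. Phase II, with half the planned effect, would be drawn in the same way.

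**Working it through.** **Inputs.** Allocation: Table 2, section 2.5.5. Clinic counts of malaria and all recorded treatments, and health posts: section 2.8.2. Clinic quotas: section 2.8.3. Planned proportions: section 2.8.1.

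**1. Reproducing the plan's own balance table.** Summing the Phase I quotas by arm gives 1,280 (no RDT) and 1,262 (RDT). The harmonic means, 11 / Σ(1/n), are 66.03 and 69.28. Both match Table 4. Health posts do not match: the printed counts give 102 and 105, against the stated 111 and 109. The drawn allocation meets all three limits with either set.

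**2. Malaria treatments by drawn arm.**

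| | No RDT | RDT |
|---|---|---|
| Kunduz | 18 / 3,445 = 0.5% | 29 / 2,456 = 1.2% |
| Nangarhar | 883 / 4,532 = 19.5% | 1,588 / 5,286 = 30.0% |
| Both, pooled | 901 / 7,977 = 11.3% | 1,617 / 7,742 = 20.9% |
| Clinic shares weighted by Phase I quota | 9.9% | 18.1% |
| Unweighted mean of clinic shares | 12.6% | 16.2% |

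The ratio of counts is 1,617 / 901 = 1.79. Total treatments are nearly equal, so balancing volume did not balance malaria.

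**3. Do the size limits protect against this?** There are 252 × 924 = 232,848 stratified allocations. On the printed data 1,958 satisfy the three limits (the protocol reports 1,598; the different health-post counts would explain a gap). A count ratio of 1.79 or more, in either direction, occurs in 10.7% of all stratified allocations and 10.5% of the acceptable ones. On the difference in unweighted clinic shares (3.6 points), 21% of acceptable allocations are at least as unbalanced.

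**4. What it could do to the outcome.** This step is an illustration under assumptions. Let p be PCR positivity, a the proportion of negatives correctly treated and q the proportion of positives correctly treated. Then correct = (1 − p)a + pq, and moving p from 0.113 to 0.209 changes it by 0.096 × (q − a). Take q from 0.5 to 0.9 (assumed), and a = 0.1 or 0.5, from the 90% and 50% of negatives expected to receive an antimalarial.

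- Arm 1 practice (a = 0.1): +3.8 to +7.7 points.
- Arm 2 practice (a = 0.5): 0 to +3.8 points.

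The planned differences are 40 points in Phase I and 20 in Phase II.

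**5. Phase II feasibility.** Half of 11 clinics is 5.5, and half of the 5 Kunduz clinics in an arm is 2.5, so the split needs a stated rounding rule. Take 3:3 in each Nangarhar group and 3:2 / 2:3 in Kunduz. This gives 2 × 10 × 10 × 20 × 20 = 80,000 allocations. Scale the Phase I limits: 50 × 6,792 / 2,542 ≈ 134 patients; 182 ± 8 for the harmonic mean (3 × 182 / 68 ≈ 8); 10 health posts. Then 612 allocations remain, of which 23% have a malaria count ratio above 1.5 (maximum 2.37). Adding a ratio of at most 1.2 leaves 274.

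**The case against.** **The largest contrast was controlled by design.** Of 2,518 malaria treatments, 2,471 are in Nangarhar, and province was a stratum. This stands: what was left uncontrolled is burden within province, and most of the gap lies inside Nangarhar.

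**This is an ordinary chance draw.** It is not an allocation error, and on unweighted clinic means, the scale nearest to a clinic-level analysis, the gap is only 3.6 points. This also stands. The counts are CHW-reported treatments and not confirmed cases, and they cover July–September 2010, whereas section 2.5.3 says its balance data are from July–December 2009. They are a proxy.

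**Adjustment belongs in the analysis plan.** Section 2.8.4 defers to one and offers its covariates only broadly, so a missing Phase I covariate is not an error in itself. But the restriction criteria and their description are fixed in the protocol, and so is their reuse in Phase II.

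**A stronger reading is tempting.** A reader might take 90% of the recorded antimalarials as wrong and all other patients as correctly untreated. That gives 1 − 0.9 × 0.209 = 81% correct in the RDT arm against 1 − 0.9 × 0.113 = 90% before any intervention, a 9-point handicap. The documents do not support it. The 90% in section 2.8.1 is the proportion of malaria-negative patients given an antimalarial, not the proportion of antimalarials that are wrong. The calculation counts URTI and diarrhoea consultations that section 2.5.7 would not enrol unless malaria was considered. It also contradicts the 10% correct treatment that the plan assumes in arm 1. The illustration above points the other way.

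**Conclusion.** The restriction factors are mislabelled. They equalise size and give no appreciable protection against imbalance in malaria burden within province. The drawn arms differ on a proxy for it: 1.79-fold on counts, 20.9% against 11.3% pooled, 16.2% against 12.6% as clinic means.

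Neither the sign nor the size of the effect on the primary outcome can be settled from the documents. Under the assumptions in the illustration it is a few points, unlikely to overturn a true 40-point Phase I difference and less negligible against 20 points in Phase II. The imbalance does not invalidate the Phase I randomisation. It does justify a prespecified adjustment and a better criterion for the second draw.

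The figures rest on the printed clinic tables. The health-post list used in the actual randomisation seems to differ from them, so the acceptable-set counts are approximate.

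**What to change.** **Phase I.** Include each clinic's baseline malaria share (malaria over total treatments, section 2.8.2) and province as covariates in a clinic-level primary analysis. Reword section 2.5.3 to say that the factors balance size and efficiency.

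**Phase II.** Randomise within province and Phase I arm: 3:3 in each Nangarhar group, and 3:2 in one Kunduz group with 2:3 in the other. Add a malaria-treatment limit to the three existing criteria. Keep the harmonic mean. If it is replaced by the malaria limit (for example at most 200 patients, 10 health posts and 200 malaria treatments, leaving 1,886 allocations), arm harmonic means range from 130 to 302 against the planned 182. With all four criteria as set out above, 274 of 80,000 allocations remain.

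**Cost.** The data are already in the protocol. The analysis spends two degrees of freedom for the two covariates: 22 − 2 = 20 become 18 (one of them extra if province was to be fitted anyway). The enumeration must be re-run with the correct health-post list.

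The smaller allocation set has a real price in validity. In the 274-allocation example, AngorBagh and Khan Abad never fall in the same arm. With a ratio limit of 1.3, 360 allocations remain and they do so in only 8. The limits given here show feasibility only. Recheck the validation matrix and loosen the limits where needed before the draw.

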### Randomisation Methods:

### Number of unrestricted allocations

The study is a stratified cluster randomised trial with a total of 22 clusters.

In Kunduz the total number of ways of allocating the 10 clusters to the two intervention groups, assuming equal number of clusters per arm:

$$\binom{10}{5}\binom{5}{5}=252$$

In Nangahar the total number of ways of allocating the 12 clusters to the two intervention groups, assuming equal number of clusters per arm

$$\binom{12}{6}\binom{6}{6}=924$$

Therefore in total there are: 252 x 924 = 232,848 possible allocations of 22 clusters into the 2 study arms after stratification.

### Exploring individual restriction factors

A compute program (R statistical environment) enumerated each of these allocations to identify which satisfy the balance criteria.

For each balance criteria, restriction factors^^[[3]](#footnote-3)^^ were estimated for various tolerance thresholds for the measure of imbalance. Table 1 presents the results for individual balance criteria in terms of the proportion of acceptable allocations and the corresponding restriction factor.

Table 1: Proportion of acceptable allocations and restriction factors for various tolerance thresholds

| **Criteria** | **Tolerance threshold** | **Proportion acceptable** | **Restriction factor** |
| --- | --- | --- | --- |
| Total sample size | 50 | 0.119 | 88.1% |
|  | 60 | 0.142 | 85.8% |
|  | 70 | 0.165 | 83.5% |
|  | 80 | 0.188 | 81.2% |
|  | 90 | 0.210 | 79.0% |
|  | 100 | 0.232 | 76.8% |
|  | 150 | 0.342 | 65.8% |
|  | 200 | 0.445 | 55.5% |
| Harmonic Mean range | 67-69 | 0.032 | 96.8% |
|  | 66-70 | 0.085 | 91.5% |
|  | 65-71 | 0.141 | 85.9% |
|  | 64-72 | 0.196 | 80.4% |
|  | 63-73 | 0.250 | 75.0% |
| Number of health posts | 5 | 0.120 | 88.0% |
|  | 6 or 7 | 0.168 | 83.2% |
|  | 8 or 9 | 0.215 | 78.5% |
|  | 10 | 0.263 | 73.7% |
|  | 15 | 0.356 | 64.4% |
|  | 20 | 0.490 | 51.0% |

### Exploring combinations of thresholds

Combinations of thresholds were examined and the final choice was based on achieving acceptable balance between the study arms and maintaining an unbiased and valid design. As described by Moulton (2004) a design is biased if there is any difference across the clusters in their probability of allocation to any given treatment. A randomised design is said to be valid if every pair of clusters has the same probability of being allocated to the same treatment. An unbiased design is unlikely to occur in practice but the validity is more questionable when conducting a constrained, or restricted, randomisation. If the design is not valid there is a risk that the Type I error changes from its nominal value of 0.05.

### Final combination of balance criteria

The final choice included the following restrictions:

1. Total sample size per arm differing by no more than 50
2. Harmonic mean in each cluster being within the range 65 to 71
3. The number of health posts per arm differing by no more than 10 health posts

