### Results of randomisation

The final choice of restriction criteria resulted in 1598 acceptable allocations from which one was randomly chosen. Table 2 and **Error! Reference source not found.** summarise the allocation process.

6 clinics (clusters) have been allocated to each study arm in the Nangahar stratum, and 5 per arm in Kunduz stratum. Study arm 0 denotes no RDT, and study arm 1 denotes RDT (intervention) – see next section.

Table 2: Results of intervention allocation process

| **Kunduz** | | |  | **Nangahar** | | |
| --- | --- | --- | --- | --- | --- | --- |
| **Cluster** | **Clinic** | **Study arm** |  | **Cluster** | **Clinic** | **Study arm** |
| 1 | Ajighan | 0 |  | 11 | Baro | 0 |
| 2 | AngorBagh | 0 |  | 12 | Batikot | 1 |
| 3 | ArbabRamazani | 0 |  | 13 | Behsood | 0 |
| 4 | BolaQachi | 1 |  | 14 | Chardhi | 1 |
| 5 | CharSari | 1 |  | 15 | GardiGhos | 1 |
| 6 | Khan Abad | 1 |  | 16 | Khewa | 0 |
| 7 | KhwajaGhaltan | 0 |  | 17 | LandaBuch | 0 |
| 8 | Madrasa | 1 |  | 18 | MamandDara | 1 |
| 9 | Nick Pay | 1 |  | 19 | NajmulQura | 1 |
| 10 | SandoqSai | 0 |  | 20 | Rodat | 0 |
|  |  |  |  | 21 | SangarSarai | 1 |
|  |  |  |  | 22 | Shegay | 0 |

Table 3: Summary of clusters allocated to study arms in Phase 1

| **Arm 0 (no RDT)** | **Arm 2 (RDT)** |
| --- | --- |
| Ajighan | Batikot |
| AngorBagh | BolaQachi |
| ArbabRamazani | Chardhi |
| Baro | CharSari |
| Behsood | GardiGhos |
| Khewa | Khan Abad |
| KhwajaGhaltan | Madrasa |
| LandaBuch | MamandDara |
| Rodat | NajmulQura |
| SandoqSai | Nick Pay |
| Shegay | SangarSarai |

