**Table 4: Examining the balance after randomisation**

|  | **No RDT (n=11)** | **RDT (n=11)** |
| --- | --- | --- |
| Total sample size | 1280 | 1262 |
|  |  |  |
| Harmonic mean number of patients per cluster | 66.03 | 69.28 |
|  |  |  |
| Number of health posts | 111 | 109 |

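### Size restrictions act on arm totals only, so planned patients are unbalanced by province, and the outlined analysis does not account for province

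*Protocol*

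**What the plan says.** Section 2.5.4 states: "The study is a stratified cluster randomised trial with a total of 22 clusters". The strata are the two provinces, and section 2.5.5 reports the outcome: "6 clinics (clusters) have been allocated to each study arm in the Nangahar stratum, and 5 per arm in Kunduz stratum".

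The final restrictions carry no province term. They are "Total sample size per arm differing by no more than 50", "The number of health posts per arm differing by no more than 10 health posts" and "Harmonic mean in each cluster being within the range 65 to 71". The last is worded by cluster, but section 2.5.3 describes the harmonic mean as a quantity per arm.

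Table 4 gives arm totals only ("Total sample size | 1280 | 1262"), and the text above it concludes that "given the above restricted randomisation we achieved a suitable balance on those factors included in the randomisation".

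Section 2.8.4 leaves the detailed analysis plan for later. It outlines a comparison of proportions by arm, with chi-square or Fisher's exact test as examples, and lists prescriber, patient and health-system covariates. Province is not among them. For Phase II, section 2.5.1 says: "A revised random allocation using the same methods will be conducted for the Phase II randomisation".

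**The concern.** Equal numbers of clinics per province do not give equal numbers of patients per province when clinic quotas run from 20 to 276. A limit on arm totals can be met by a surplus in one province that offsets a deficit in the other, and a table of arm totals cannot show this.

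Province is likely to matter for the primary outcome. Section 2.2 says that malaria incidence is higher in the East. Among the treatments listed in section 2.8.2, malaria makes up 47/5901 = 0.8% in Kunduz and 2471/9818 = 25.2% in Nangarhar. Correct treatment is scored by different rules for PCR-positive and PCR-negative patients, so the mix of provinces could move the proportion correctly treated. If the arms hold different mixes and the comparison ignores province, part of any provincial difference is counted as an effect of the RDT.

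**Working it through.** **Inputs.** Phase I quotas weighted to a harmonic mean of 68 (section 2.8.3 table) and the allocation in Table 2 (section 2.5.5).

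**Reproducing Table 4 by province.**
- Kunduz, no RDT: 124 + 276 + 25 + 112 + 107 = 644
- Kunduz, RDT: 112 + 88 + 249 + 51 + 20 = 520
- Nangarhar, no RDT: 63 + 122 + 185 + 95 + 20 + 151 = 636
- Nangarhar, RDT: 205 + 36 + 130 + 142 + 114 + 115 = 742

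The arm totals are 644 + 636 = 1280 and 520 + 742 = 1262, as Table 4 states. Harmonic means, 11 / Σ(1/n), are 66.03 and 69.28, also as stated.

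**What the totals conceal.** Kunduz has 644 − 520 = 124 more control patients. Nangarhar has 742 − 636 = 106 more RDT patients. The net difference is 18. Harmonic means within province are 71.5 against 53.2 (Kunduz) and 62.1 against 92.5 (Nangarhar). Kunduz shares are 644/1280 = 50.3% and 520/1262 = 41.2%, a gap of 9.1 points.

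**Level at which the limits were applied.** Enumerating all 252 × 924 = 232,848 allocations with limits on arm totals returns the Table 1 proportions for sample size (0.119 at 50, 0.445 at 200) and harmonic mean (0.141 at 65–71). The limits were therefore not applied within province.

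**How typical the draw is.** With the listed quotas and health posts, 1958 allocations meet the three criteria. Among them the Kunduz difference has median 104 and maximum 534, and 216 (11%) keep both provinces within 50. The protocol reports 1598 acceptable allocations, and its 111 + 109 = 220 health posts do not match the 207 listed, so the enumeration is not an exact replica. The patient figures above do not depend on it.

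**Size of the shift.** Let w be an arm's Kunduz share and suppose the RDT effect is the same in both provinces. Then

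crude difference (RDT − no RDT) = true effect + (w_control − w_RDT) × (Nangarhar rate − Kunduz rate).

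Here w_control − w_RDT = 0.091. The provincial gap is an assumption:
- 10 points: 0.091 × 10 = 0.9 points
- 20 points: 0.091 × 20 = 1.8 points

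The direction depends on which province has the higher rate.

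**A ceiling on the gap in Phase I.** Section 2.8.1 plans 10% correct treatment in the control arm. If one province were at 0%, the other would be at about 0.10/0.50 = 20%. A control-arm gap much above 20 points does not fit the planning figures.

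**The case against.** The strongest defence is that nothing here contradicts the protocol's own aims. Section 2.5.3 restricts on size for precision and power per arm, and the claim of suitable balance covers only the factors that were restricted. Province is handled by stratifying clinics. The imbalance is chance: the median gap in Kunduz share is 9.5 points over all unrestricted allocations and 8.3 among the accepted ones, so the restrictions did not cause it. The leak needs an analysis that weights by patient and ignores province. A province-adjusted analysis or an unweighted cluster-level summary removes it, and the analysis plan is still to be written. The shares are also quotas, not achieved enrolment.

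All of that stands. What remains is that the analysis outlined in section 2.8.4 is of the exposed kind, and its covariate list leaves out the factor on which the trial was stratified.

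Three stronger readings are tempting and are not supported:
- A reader might infer a systematic bias against one arm. The allocation was drawn at random from a set whose criteria treat the arms alike, so there is none in expectation.
- A reader might take 0.8% against 25.2% as the provincial gap in the outcome and expect shifts of several points. Those figures are shares of recorded treatments, not PCR prevalence or correct-treatment rates among enrolled patients, and gaps of 40 or 80 points conflict with a 10% control rate.
- A reader might conclude that Phase II should simply impose the limits within province. With Phase II quotas, limits of 150 patients and 10 posts per province leave 552 allocations, but these use only 6 of the 252 Kunduz allocations and put 17 of the 45 Kunduz pairs at probability 0 or 1. Splitting by Phase I arm (read as 2/3 in Kunduz and 3/3 in Nangarhar) leaves 152 allocations and 29 such pairs. That fails the validity test in sections 2.5.4 and 2.5.5.

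**Conclusion.** The point holds in a limited form. The planned arms differ by 9.1 points in their Kunduz share, and Table 4 cannot show it. The consequence depends on the analysis: a patient-weighted, province-unadjusted comparison shifts by about 0.9 to 1.8 points if the provinces differ by 10 to 20 points in correct treatment. That is small against the 40 points expected in Phase I. In Phase II the expected difference is 20 points, so a shift of the same size would weigh twice as much in relative terms. The Phase II allocation is not yet drawn, however, and its share gap may be smaller or larger. The result rests on the quotas being filled as planned, a common RDT effect across provinces, and an assumed provincial gap.

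**What to change.** 1. In section 2.8.4, state that in both phases the arm comparison is stratified by or adjusted for province, either at cluster level or by another method that allows for clustering. This follows the randomisation and removes the leak. It needs no new data. In a cluster-level analysis, adding province costs one degree of freedom (22 − 2 = 20 becomes 22 − 3 = 19).
2. Show Table 4 by province, and describe the balance achieved as balance of arm totals.
3. Do not adopt within-province limits of 150 patients and 10 posts for Phase II. Use any within-province limit only if the validation matrix of section 2.5.5, rerun after the split by Phase I arm in section 2.5.6, shows no pair of clinics at or near 0 or 1. The cost is one further enumeration.
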